### Outcome Assessment

The primary outcome is the change in functional status during the study period.•The functional capacity of participants is evaluated by the Short Physical Performance Battery (SPPB) (22), with the total score ranging from 0 (worst) to 12 points (best). This test evaluates balance, gait and rising from a chair. The standing balance test consists of the evaluation of the ability to maintain the standing position for 10 seconds with three different feet-positions: parallel, semi-tandem and tandem. The walking speed test measures the time needed to progress for 4 linear meters at the patient's usual speed, assigning a different score according to speed. Finally, the chair sit-to-stand part assesses the ability to stand from a chair five consecutive times without using the arms. The SPPB test has been shown to be a valid instrument for screening frailty and predicting disability, institutionalization and mortality.

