
### Statistical procedures

The sample size calculation was performed using the GPower v. 3.1 software, adopting a significance level of α = 5%, a correlation between pre-and post-intervention values of the Short Physical Performance Battery (SPPB) of ϱ = 0.5 and a standard deviation for the SPPB of σ = 2.5, the required sample size to have a power of 90% to detect a minimum difference of 1 point between groups in the post–pre SPPB score is 101 patients per group. Taking an expected loss of patients at follow-up of 15% into account, the final sample size required is 120 per group.

The description of the sample by the group will be conducted using statistics such as means and standard deviations or medians and interquartile ranges for the quantitative variables, and frequencies and percentages for the qualitative variables. For comparisons between groups at baseline, t-tests or Mann–Whitney U tests will be used for continuous variables, depending on normality, which will be checked for each using the Kolmogorov-Smirnov test and normal probability plots, and the chi-square test or Fisher's test will be used for categorical variables.

To determine the efficacy of the intervention in the quantitative variables, such as the SPPB, we will use linear mixed models, using time, group and time and group interaction as categorical covariates. In the case of qualitative or categorized variables (such as whether an improvement of a given magnitude between pre-and post-intervention has been achieved or not), comparisons between groups will be conducted with the chi-square test or Fisher's test, and complemented with logistic regression if additional adjustment is needed. Effect sizes between-group will be computed based on Cohen's d and the 95% confidence interval. The level of statistical significance will be 0.05. Data will be analyzed using an intention-to-treat approach with R and SPSS statistical packages.

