## Initial results

Patients show a mean age of 74.4 years (SD 5.3), mostly men (60%) and frail (Short Physical Performance Battery (SPPB)) around 8.5 (see supplement Table S1). This population is younger than in previous studies by our research group in geriatric wards, but at the same time shows a profile of frailty according to different variables like SPPB, hand grip, gait speed or functional measures.

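### The improved-or-not comparisons use an unadjusted chi-square or Fisher test; adjusting for the baseline score would recover a modest amount of power in this supporting analysis

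*Protocol article*

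**What the plan says.** The Statistical procedures section of the protocol article separates two kinds of outcome.

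- Quantitative variables, with the SPPB as the example, go into a linear mixed model with time, group and their interaction.
- Qualitative or categorised variables are handled differently. The example given is "such as whether an improvement of a given magnitude between pre-and post-intervention has been achieved or not". For these, "comparisons between groups will be conducted with the chi-square test or Fisher's test, and complemented with logistic regression if additional adjustment is needed".

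So the unadjusted test is the stated comparison, and a logistic model is an optional addition to it.

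Three other places bear on the point. Outcome Assessment gives the SPPB a range of 0 to 12. Initial results describes the patients as "frail (Short Physical Performance Battery (SPPB)) around 8.5". Table 2 lists the SPPB at T1, so the baseline value is collected as a matter of course.

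**The concern.** A patient counts as improved or not according to the difference between two scores, and the first of those scores carries much of the information about the answer. Patients who start low tend to gain. Patients who start at or near the top of the scale can gain little or nothing, whichever arm they are in. A test that looks only at the two proportions treats this predictable variation as noise. The price is power in the improved-or-not comparison. The section already allows for a logistic model, but only as a conditional extra, so the more efficient analysis is not the one that the plan commits to.

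**Working it through.** **Inputs from the document.** Statistical procedures gives "a standard deviation for the SPPB of σ = 2.5" and "a correlation between pre-and post-intervention values of the Short Physical Performance Battery (SPPB) of ϱ = 0.5", and states that the number needed for "a power of 90% to detect a minimum difference of 1 point between groups in the post–pre SPPB score is 101 patients per group". The scale maximum is 12 (Outcome Assessment) and the baseline mean is about 8.5 (Initial results).

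**Assumptions.** The article gives no improvement cut-off, so gains of at least 1 and at least 2 points are both shown. The 5% level is taken as two-sided. The SD of 2.5 is applied at both visits, and scores are drawn as bivariate normal.

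**1. The plan's own sample size.** With the baseline-adjusted SD, 2.5 × √(1 − 0.5²) = 2.165, n per group = 2 × (1.960 + 1.282)² × 2.165² / 1² = 98.5, so 99 (100 with the t distribution). The stated figure is 101. With the change-score SD, 2.5 × √(2 × (1 − 0.5)) = 2.5, the same formula gives 131.3, so 132. The stated figure therefore sits close to a calculation that already credits baseline SPPB with explaining part of the outcome.

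**2. How strongly baseline predicts change.** With equal SDs, corr(baseline, change) = (ρ − 1) / √(2(1 − ρ)) = (0.5 − 1) / √1 = −0.5.

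**3. The ceiling.** With scores rounded to whole points, the share starting at 12 is 1 − Φ((11.5 − 8.5)/2.5) = 1 − Φ(1.2) = 11.5%. These patients cannot gain 1 point. The share starting at 11 or 12 is 1 − Φ((10.5 − 8.5)/2.5) = 1 − Φ(0.8) = 21%. These cannot gain 2. In simulated controls, the chance of gaining at least 1 point falls from 80% at a baseline of 4 to 46% at 8, 28% at 10 and 0% at 12.

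**4. Power.** The simulation used 3,000 trials per setting and a 1-point effect. It compared the Pearson chi-square without continuity correction against the Wald test from a logistic regression on group and baseline SPPB. Monte Carlo error is about √(0.5 × 0.5 / 3000) = 0.9 percentage points per figure.

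| Per group | Improvement | Scores | Chi-square | Logistic with baseline | Gain (points) |
|---|---|---|---|---|---|
| 101 | ≥ 1 | rounded, 0–12 | 58.1% | 65.5% | 7.4 |
| 101 | ≥ 2 | rounded, 0–12 | 48.4% | 58.7% | 10.3 |
| 101 | ≥ 1 | unbounded | 63.0% | 68.4% | 5.4 |
| 101 | ≥ 2 | unbounded | 56.9% | 62.5% | 5.6 |
| 40 | ≥ 1 | rounded, 0–12 | 26.9% | 31.0% | 4.1 |
| 40 | ≥ 2 | rounded, 0–12 | 22.9% | 28.1% | 5.2 |
| 40 | ≥ 1 | unbounded | 28.9% | 31.0% | 2.1 |
| 40 | ≥ 2 | unbounded | 26.7% | 28.9% | 2.2 |

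A second run of 2,000 trials per setting at 101 per group gave gains of 9.4 and 9.6 points (bounded) and 5.5 and 7.0 points (unbounded). As a closed-form check on the unbounded case, the control proportion gaining at least 1 point is 1 − Φ(1/2.5) = 34.5% and the intervention proportion is 50%. The simulated values are 34.4% and 50.2%.

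**5. Validity.** With no true effect, the chi-square rejected in 4.3% to 5.6% of trials and the logistic test in 4.0% to 5.5%. Neither test is liberal, so the gain in power is real.

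**6. Sensitivity to the correlation.** With bounded scores, a gain of at least 1 and 101 per group, ρ = 0.7 gives 75.5% against 80.7%, and ρ = 0.8 gives 89.7% against 92.1%. The gain shrinks to about 5 and 2 points.

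**7. The sample now expected.** The Discussion reports recruitment of one-third of the initial estimate: 101/3 ≈ 34 evaluable or 120/3 = 40 enrolled per group. Over that range the gain is about 0 to 5 points.

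**The case against.** The case against is strong in several respects.

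- **The planned test is sound.** An unadjusted comparison of two randomised proportions is standard and holds its level. A chance baseline imbalance of one standard error, 2.5 × √(2/101) = 0.35 points, would move the difference in improved proportions by about 0.35 × 0.5 / 2.5 × 0.39 ≈ 3 percentage points. That is ordinary sampling variation, which the test and its interval already cover. It is not bias. This stands.
- **The analysis is minor.** No improved-or-not SPPB outcome appears among the listed endpoints. It is an example in the methods text, beside a mixed model that carries the SPPB result. This stands and limits the importance of the point.
- **The unspecified details may be elsewhere.** The cut-off, the covariates and the condition for adjusting are commonly left to a full protocol or an analysis plan. Their absence from an article is not counted here. What remains is that the article does name the unadjusted test as the comparison.
- **The larger gains belong to a sample that will not be reached.** This stands, and the smaller range is given above.

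A reader might also infer that the conditional wording lets the analyst see both results and report the better one. If either test could be claimed, type I error would rise to about 6% to 8%. The document does not support that reading. It says that the logistic model complements the chi-square or Fisher test, so the latter is always run and stays the main comparison. The section also plans baseline significance tests, but it does not tie the adjustment to them. Group codes are withheld from those processing the data until the coded analysis is complete.

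**Conclusion.** The point holds as a modest gain in efficiency, not as an error. The unadjusted test is valid, but it leaves out a measured variable that correlates −0.5 with change under the plan's own inputs and that, through the ceiling, limits who can improve. The loss is about 5 to 10 points of power at 101 per group and about 0 to 5 points at 34 to 40 per group. At 40 per group neither test exceeds about 31%, so adjustment does not rescue the comparison.

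These figures rest on cut-offs of 1 and 2 points, equal SDs at both visits, and normal scores that are then rounded and bounded. The article's text gives no observed distribution of baseline SPPB, so the shares starting too high to improve are modelled, not observed. A higher pre-post correlation makes the gain smaller. The primary mixed model and the sample size are untouched.

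**What to change.** In Statistical procedures, state that each improved/not-improved variable is analysed mainly by logistic regression on group and the baseline value of the same measure (baseline SPPB for SPPB improvement), in every case. Report the marginal difference in proportions with its 95% confidence interval. Keep the chi-square or Fisher test as a descriptive supplement, and delete the clause that makes adjustment conditional.

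The cost is a sentence or two of text and slightly more analysis work; no new data are needed. The odds ratio from such a model is conditional on baseline, and reporting the marginal difference deals with that. The article places the baseline assessment after randomisation, so the wording should require a value taken before the first exercise session. The change that defines improvement already relies on that same measurement.

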After randomization, the research team (physiotherapist, sport science specialist, oncologist, and geriatrician) perform the baseline measurement and follow-up visits of functional, pharmacological, comorbidity, and cognitive assessment, as well as mobility and strength evaluations (Table 2). The multidisciplinary research team has previous experience in functional geriatric assessment and in the prescription of exercise in frail older patients in different clinical settings (12, 21). Regarding oncogeriatric patients, our previous findings confirm that a multicomponent exercise program improves measures of physical/cognitive functioning and quality of life in older adults with lung cancer under adjuvant therapy or palliative treatment, and some systematic reviews identify the best options and challenges in these type of patients (43, 44, 45, 46).

**Table 2 Tab2:** Time of measurement of the different variables in each of the participants of the study

**Measurement**	**T1 Baseline**	**T2 After training or control period**	**T3 1-month post decharge**	**T4 3-months post decharge**
Categorical scale of pain	x	x	x	x
Handgrip strength	x	x	x	x
Barthel Index	x	x	x	x
Karnofsky's Index	x	x	x	x
Geriatric depression Scale of Yesavage (GDS)	x	x	x	x
Short Physical Performance Battery (SPPB)	x	x	x	x
Gait Velocity Test (GVT)	x	x	x	x
Dual-task (verbal and arithmetic GVT)	x	x	x	x
Maximal isometric force of handgrip	x	x	x	x
1RM (Leg press, Chest press and Knee extension)	x	x	x	x
Muscle power at 50 % 1RM in Leg press	x	x	x	x
Quality of Life (EQ-5D-5L)	x	x	x	x
EORTC QLQ-C30	x	x	x	x
Geriatric syndromes	x	x	x	x
Brief Fatigue Inventory	x	x	x	x
Trail Making Test part A (TMT-A)	x	x	x	x
Laboratory parameters	x	x		
Diseases considered grouped by ACG of Salisbury and CIE-10 codes	x			
Cumulative Illness Rating Scale for Geriatrics (CIRS-G)	x			
Falls	x	x	x	x
Mini Nutritional Assessment (MNA)	x	x		

1RM: 1 Repetition Maximum;

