Secondary outcomes of the study will include:•Handgrip strength. Handgrip strength is a useful tool for the measurement of functional capacity and predictor of disability (23). Each study participant will be asked to squeeze the dynamometer (Takei 5401 Digital Dynamometer) two different times and the higher score will be used to reflect handgrip strength. The measurement will be performed while the participant is seated, with the dominant hand with the elbow straight and the shoulder abducted at 15° (24, 25).•Changes in functional capacity in activities of daily living (ADLs) as measured with the Barthel Index (Spanish version) scale, which ranges from 100 (functional independence) to 0 (severe functional dependence) (26). This is an international, validated tool and it is the most used to measure disability (27).•Karnofsky' Index: The Karnofsky Performance Status (KPS) is a widely used method to assess the functional status of a patient.•Gait ability will be assessed using the 6-meter gait velocity test (GVT). Starting and ending limits will be marked on the floor with tapelines for a total distance of 8 m. Participants will be instructed to walk at their self-selected usual pace for two attempts. The results of both trials will be averaged to obtain a single value. The first and last meters, considered the warm-up and the deceleration phases, respectively, will not be included in the calculations of the gait assessment.•Dual-task GVT (arithmetic GVT). During the arithmetic dual-task arithmetic test (arithmetic GVT), we will assess the gait velocity while participants are counting backwards aloud from 100 one at a time. The cognitive score will be measured by determining how many numbers were counted backward (dual-task with arithmetic performance) (28).•Changes in mood status: the 15-item Yesavage Geriatric Depression Scale (GDS-VE), the Spanish Version, contains ten affirmative and five negative items, its score being normal when it ranges from 0 to 5 and a score greater than 5 suggesting depression (29).•Changes in the Trail Making Test (TMT) part A will be evaluated to assess executive dysfunction. The TMT is one of the most popular neuropsychological tests and is included in most test batteries. TMT-A requires an individual to draw lines sequentially connecting 25 encircled numbers distributed on a sheet of paper (30).•Maximal dynamic strength will be assessed using the 1RM test in the bilateral leg press, knee extension and bench press exercises using exercise machines (Matrix, Johnson Health Tech, Ibérica, S.L., Madrid, Spain). In the first assessment, the subjects will warm up with specific movements for the exercise test. Each subject's maximal load will be determined in no more than five attempts, with a 3-minute recovery period between attempts. During all neuromuscular performance tests, strong verbal encouragement will be given to each subject to motivate them to perform each test action as optimally and rapidly as possible. Qualified fitness specialists will individually monitor and carefully supervise all training sessions and provide instruction and encouragement during all sessions.•Changes in the quality of life will be measured by the Spanish version (31) of the EuroQol–5 Dimension (EQ-5D) questionnaire (32). It is an instrument that measures 5 dimensions of health status: mobility, self-care, usual activities, pain/discomfort, and anxiety/depression. Each dimension is rated according to the following levels: a) no problems; b) some problems; c) extreme problems. Besides, it contains a visual analogy scale to quantify the self-perceived health status, ranging from 0 (worst health state imaginable) to 100 (best health state imaginable).•Number of days alive after admission to the hospital.•Use of health resources: new admissions to the hospital, admission to nursing homes, visits to the emergency department and visits to the general practitioner.•Visual analogue scales (VAS) typically ask a patient to mark a place on a scale that matches their level of pain (33);•Mini-nutritional assessment- short form (MNA-SF): evaluation of nutritional status (34).•Brief Fatigue Inventory: validated tools to measure fatigue in patients with cancer (35).

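### For categorical efficacy outcomes the plan names only order-blind tests; if the pain categories and EQ-5D levels follow that rule, power and direction are lost (secondary outcomes only)

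*Protocol article*

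**What the plan says.** Statistical procedures sorts efficacy outcomes into two classes. For quantitative variables, with the SPPB as the example, "we will use linear mixed models, using time, group and time and group interaction as categorical covariates". For qualitative or categorized variables, "comparisons between groups will be conducted with the chi-square test" or Fisher's test, and logistic regression is added only where adjustment is called for. The only example given for the second class is binary: "such as whether an improvement of a given magnitude between pre-and post-intervention has been achieved or not". Mann–Whitney appears elsewhere, for baseline comparisons and for adverse events, but not for efficacy. The one effect size named is Cohen's d.

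Two secondary outcomes have ordered categories on the article's own description:

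- **Pain.** Table 2 has the row "Categorical scale of pain", measured at all four times. Outcome Assessment describes a different instrument: "Visual analogue scales (VAS) typically ask a patient to mark a place on a scale that matches their level of pain".
- **EQ-5D.** Outcome Assessment states: "Each dimension is rated according to the following levels: a) no problems; b) some problems; c) extreme problems". The same item adds a 0–100 self-rated health scale. Table 2 names the five-level version of the questionnaire instead.

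**The concern.** The question for pain and for each EQ-5D dimension is directional: did patients move towards better or worse levels? Pearson's chi-square and Fisher's test treat the levels as unordered labels. Relabelling or shuffling the levels leaves the p-value unchanged. With k levels, chi-square spreads its sensitivity over k − 1 degrees of freedom, although a shift along the scale needs only one.

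Two things follow if an ordered outcome is tested this way. A real shift is detected less often. And a significant result need not mean that either arm did better, because a difference in spread alone can produce it. Cohen's d does not repair this for a table of categories. Recruitment is also reported at about one third of plan, so there is little power to spare.

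**Working it through.** **Inputs from the article.** Alpha is 5% (two-sided assumed). The target is 101 evaluable patients per arm. Recruitment stands at one third of 240, so 240/3 = 80, or 40 per arm if allocation is equal, before any losses.

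The 101 can be reproduced. With SD 2.5 and correlation 0.5, the baseline-adjusted SD is 2.5 × √(1 − 0.5²) = 2.165, and n = 2 × (1.960 + 1.282)² × 2.165² / 1² ≈ 99 per arm (100 with the t distribution). A raw change-score SD of 2.5 would give 132. That is a separate matter: here 101 serves only as the planned arm size, and the article gives no power figure for any ordered outcome.

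**Assumptions.** The article gives no level distribution, no number of pain categories and no expected effect. All of these are assumed: three, four or five levels, and a common odds ratio (OR) for being at or below each cut-point.

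**Worked case: four equal levels, OR 2, 101 per arm.**

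1. The control cumulative proportions are 0.25, 0.50 and 0.75, so the odds are 1/3, 1 and 3. Doubled, they are 2/3, 2 and 6, which give 0.400, 0.667 and 0.857.
2. The intervention level proportions are therefore 0.400, 0.267, 0.190 and 0.143.
3. For equal arms the chi-square noncentrality is n × Σ(p − q)²/(p + q) = 101 × (0.0346 + 0.0005 + 0.0080 + 0.0292) ≈ 7.3 on 3 degrees of freedom. The critical value is 7.81 and the power is 61%. The order of the terms in the sum plays no part.
4. Simulation (40,000 trials) gives 61% for chi-square and 78% for the tie-corrected Mann–Whitney test on the same tables.

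**All cases at OR 2** (power, chi-square against Mann–Whitney):

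| Levels | Assumed control distribution | 101 per arm | 40 per arm |
|---|---|---|---|
| 3 | 40/45/15% or equal thirds | 62–66% vs 72–75% | 29–31% vs 36–38% |
| 4 | equal quarters | 61% vs 78% | 26% vs 40% |
| 5 | 30/25/20/15/10% or equal fifths | 56–58% vs 77–79% | 22–24% vs 39–41% |

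The loss is about 10, 16 and 21 points at 101 per arm, and about 8, 13 and 17 points at 40. Both tests hold a type I error near 5%.

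**Other effect sizes at 101 per arm.** At OR 1.5: 25–27% against 33–34% (three levels), 24% against 36% (four) and 21% against 36–37% (five). At OR 2.5: 86–88% against 92–93%, 87% against 95% and 82–84% against about 95%.

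**Significance without direction.** Take 30/40/30% against 40/20/40%. The chance that a patient from the second arm is at a better level, counting ties as half, is 0.4 × 0.85 + 0.2 × 0.50 + 0.4 × 0.15 = 0.50, so neither arm is better. The chi-square noncentrality is 101 × (0.01/0.7 + 0.04/0.6 + 0.01/0.7) = 9.6 on 2 degrees of freedom. In simulation chi-square is significant in 81% of trials at 101 per arm and 40% at 40 per arm. Mann–Whitney is significant in about 5% at either size.

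**Binary check.** With 50% against 68% at 101 per arm, both tests have 75% power. Nothing is lost for the article's own example.

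**The case against.** The strongest reply is that the article never says pain or EQ-5D levels will be tested by chi-square. Its one example is binary, where chi-square is suitable. It treats the SPPB, a summed 0–12 score, as quantitative, so other ordered scores might also go to the mixed model. Pain by visual analogue scale and the EQ-5D 0–100 scale would certainly go there. No dimension-by-dimension EQ-5D comparison is declared as an endpoint. A condensed article may leave the matching of instruments to methods to an analysis plan.

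Most of this stands, and it makes the point conditional. It does not remove it. The binary case is offered as an example and does not limit the class. The article positively fixes a rule for categorical outcomes, and that rule contains no ordered method. A row labelled as a categorical scale falls under it on a plain reading.

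Three stronger readings are tempting, and the article does not support them:

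- That chi-square or Fisher is the only method. Logistic regression is also named, although only where adjustment is needed and not in an ordinal form.
- That a planned conclusion on quality of life rests on this test. The Discussion only speculates that quality of life may improve if guidelines change.
- That the main result is at risk. The SPPB is analysed by mixed model.

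The no-direction pattern was built to show the mechanism, and nothing in the article makes it likely. The gain was simulated for a single-time rank test, not for a repeated-measures ordinal model.

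**Conclusion.** The point holds in conditional form and is minor. The rule for categorical efficacy outcomes names order-blind tests as the main comparison and no ordered alternative. If the pain categories or EQ-5D levels follow it, the cost at OR 2 and 101 per arm is roughly 10 to 21 points of power, rising with the number of levels, and a significant result need not favour either arm. The sizes rest on assumed distributions and odds ratios. The direction of the loss is the same in every shifted scenario examined. Whether the rule is applied to pain at all cannot be settled from the article, because Table 2 and Outcome Assessment describe different pain scales. The number of EQ-5D levels is unsettled in the same way.

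**What to change.** In Statistical procedures, restrict chi-square or Fisher's test to binary and nominal variables. State that ordered categories are analysed by an ordered method: Mann–Whitney, or a proportional-odds model reporting a common odds ratio with its 95% confidence interval. In the same edit, reconcile the pain scale (categorical in Table 2, visual analogue in Outcome Assessment) and the EQ-5D version (five-level in Table 2, three levels in Outcome Assessment), and say which form of each is analysed.

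The cost is a sentence or two. Data collection does not change once the instruments are reconciled, and R, which the article already names, can fit these methods. The one added task is checking the proportional-odds assumption if that model is chosen. If a repeated-measures version is preferred, its convergence at about 40 per arm has not been examined here, so Mann–Whitney should be named as the fallback.

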**Methods:**

We present the research protocol for a randomized controlled trial that will analyze whether an intervention applied to older patients (≥ 65 years) who are hospitalized for acute medical conditions in an Oncology Department improves function. A total of 240 hospitalized older patients will be recruited in the Hospital Universitario de Navarra, Pamplona, Spain, and they will be randomized. The intervention consists of a multicomponent exercise training program that will take place for 4 consecutive days (2 sessions/day). The control group will receive usual hospital care, which will include physical rehabilitation when needed. The primary end point will be the change in functional capacity from baseline to hospital discharge, assessed with the Short Physical Performance Battery (SPPB). Secondary end points will be changes in cognitive and mood status, quality of life, fatigue, strength (dynamic and handgrip), pain, nutrition, length of stay, falls, readmission rate and mortality at 3 months after discharge.

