In order to check the assumption that the potential impact of missing data is negligible (created by a missing complete at random or a missing not at-random mechanism), best–worst and wors`t-best case sensitivity analyses will be used. When the missing data surpasses 5% and if this is supported by the previous sensitivity analysis, a missing at-random mechanism will be assumed and missing values will be imputed using the R package MICE (Multivariate Imputation via Chained Equations). If the proportion of missing data is very large (rises over 40%) on important variables, trial results will be considered hypothesis-generating results.

We will compare the proportion or number of adverse events between groups, using chi-square test or Mann-Whitney U test.

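### Best-worst and worst-best bounds cannot support a missing-at-random assumption, so they should not decide whether SPPB is imputed

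*Protocol article*

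**What the plan says.** The missing-data rule stands at the end of Statistical procedures in the protocol article and has three steps.

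1. Best-worst and worst-best analyses are run first. Their purpose is introduced with "In order to check the assumption that the potential impact of missing data is negligible (created by a missing complete at random or a missing", and the sentence goes on to name the not-at-random case.
2. A gate follows: "When the missing data surpasses 5% and if this is supported by the previous sensitivity analysis, a missing at-random mechanism will be assumed". If it is passed, "missing values will be imputed using the R package MICE".
3. An upper limit applies: "If the proportion of missing data is very large (rises over 40%) on important variables, trial results will be considered hypothesis-generating results".

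No extreme values are defined for the scenarios, no criterion for support is given, and no action is stated if support is lacking.

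Elsewhere, the same section plans a linear mixed model for SPPB with time, group and their interaction. It sizes the trial with "Taking an expected loss of patients at follow-up of 15% into account". Table 2 schedules SPPB at baseline, after the training or control period, and at 1 and 3 months after discharge. The abstract defines the primary endpoint as change from baseline to discharge and lists among the secondary endpoints "readmission rate and mortality at 3 months after discharge".

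**The concern.** The gate asks an analysis a question it cannot answer. A best-worst scenario replaces missing values by favourable values in one arm and unfavourable values in the other; worst-best reverses this. The gap between the two depends on how much is missing and which extremes are chosen. The reason why values are missing does not enter. MAR and MNAR cannot be told apart from observed data, and bounds of this kind do not change that.

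Two consequences follow. First, the scenarios need outcome data by arm, so whether SPPB is imputed is settled after results have been seen, against a criterion that nobody has written down. Second, a trial that passes the gate could report MAR as having been checked, although no MNAR analysis beyond the crude bounds is planned.

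**Working it through.** **The plan's own figures.** The missing-data rule contains only thresholds (5% and 40%), so there is nothing in it to reproduce. The 15% loss comes from the sample size:
- With SD 2.5 and correlation 0.5, the baseline-adjusted SD is 2.5 × √(1 − 0.5²) = 2.165. For a 1-point difference, two-sided 5% (sidedness is not stated; two-sided assumed) and 90% power, this gives 99 to 100 per group, against 101 stated.
- 101 / 0.85 = 118.8, so 119, against 120 stated.
- 15% of 240 is 36 patients. 15% is three times the 5% trigger.

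**Width of the bounds.** Inputs: SPPB range 0 to 12 (Outcome Assessment), SD 2.5 and target difference 1 (Statistical procedures). Let f be the fraction missing, equal in both arms, and d the difference among observed patients.
- Extremes 0 and 12: bounds = (1 − f)d ± 12f, spread = 24f.
- Extremes 1 SD above and below each arm's observed mean (assumed): bounds = d ± 5f, spread = 10f.

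With d = 1:

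| f | 0/12 bounds | spread | ±1 SD bounds | spread |
|---|---|---|---|---|
| 5% | +1.55, +0.35 | 1.2 | +1.25, +0.75 | 0.5 |
| 15% | +2.65, −0.95 | 3.6 | +1.75, +0.25 | 1.5 |
| 40% | +5.40, −4.20 | 9.6 | +3.00, −1.00 | 4.0 |

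At 15%, one choice of extremes gives bounds of opposite sign and the other keeps both positive. The same data could therefore be read either way.

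**Do the bounds respond to the mechanism?** A simulation used 2000 runs, 120 per arm, 15% missing overall, baseline mean 8.5 (Initial results), SD 2.5, correlation 0.5, and an effect of 1 point before truncation to 0–12. Missingness was completely at random (MCAR), dependent on baseline (MAR), or dependent on the unseen outcome (MNAR). The strength of dependence is an assumption. Extremes were 0 and 12.

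| Mechanism | Full-data estimate | Observed-data estimate | Best-worst | Worst-best | Spread |
|---|---|---|---|---|---|
| MCAR | 0.88 | 0.88 | +2.56 | −1.05 | 3.61 |
| MAR | 0.87 | 0.86 | +2.53 | −1.07 | 3.60 |
| MNAR | 0.88 | 0.78 | +2.60 | −0.99 | 3.59 |

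Under MNAR the observed-data estimate falls 0.10 below the full-data value, yet the bounds differ from the MCAR bounds by only 0.04 and 0.06. In one trial the standard error of the difference is about 2.165 × √(2/120) = 0.28 even with complete data, so gaps of that size could not be seen.

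**The possible readings of the gate.** The condition can be read in three ways.
- The scenarios must support MAR: they cannot.
- They must show negligible impact: MICE is then used only when it hardly matters, and nothing is planned when it does.
- They must show that the impact is not negligible: MAR is then assumed exactly where the result is most sensitive to it.

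None of the three gives a valid basis for assuming MAR.

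**The case against.** The strongest reply is that the authors probably meant the third reading: if the impact is not negligible, impute. That is a sensible motive, but it still supplies no ground for MAR and leaves the other branch undefined.

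Further points on the other side have weight:
- The mixed model for SPPB is fixed without condition, so a reader who infers that the whole primary analysis is open goes too far. What is open is whether imputed or observed data enter it. The coded group labels described under randomization reduce conscious bias, but the choice still depends on results.
- A reader might infer that the check can never be passed, or that the bounds always exceed the target. The documents do not support this, because the extremes are undefined. With ±1 SD at 15% missing, the estimate moves by only 0.75 either way.
- A reader might infer that the plan declares MNAR harmless. It only proposes to check that the impact is negligible.
- A reader might infer that SPPB will be imputed for patients who died. No sentence says so; that would be drawn from silence, and a condensed article may leave the handling of death to a fuller document. The primary endpoint ends at discharge and terminal illness is an exclusion, so the matter concerns mainly the 1- and 3-month visits. No death rate is given, so it cannot be sized.
- A mixed model on observed data also assumes MAR. This stands in full, and it is why the remedy needs an explicit MNAR analysis.

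**Conclusion.** The point holds for the gate itself. This is a stated rule, not an omission, and it rests an untestable assumption on an analysis with no bearing on it. If 15% of SPPB values are missing equally in both arms, the bounds lie 3.6 points apart with extremes of 0 and 12, or 1.5 points apart with ±1 SD, against a 1-point target. Both spreads exceed the target, but the conclusion about sign differs between them.

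This assumes that the 15% applies at the visit analysed. Loss by discharge could be lower, in which case the trigger might be met only at later visits. The argument that bounds cannot support MAR needs no figure at all.

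On death, the supportable statement is narrow and secondary: the rule as written does not separate death from other missing SPPB values.

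**What to change.** - Delete the condition that makes MAR and MICE depend on the extreme-case results, together with the 5% trigger.
- State that the primary analysis is the linear mixed model already planned, fitted to all observed SPPB visits under MAR whatever the percentage missing.
- Make MICE a supportive analysis.
- Add a delta-adjusted tipping-point analysis by arm, showing how much worse the missing SPPB values would have to be to change the conclusion.
- Keep best-worst and worst-best only as outer bounds, with the extreme values defined in advance.
- Report deaths by arm. For the 1- and 3-month visits, add a sensitivity analysis that does not treat SPPB after death as ordinary missing data. Any score given to death is a convention, so show that result beside the model-based estimate.

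The cost is a rewritten paragraph and modest extra analysis. Nothing changes in data collection or sample size.
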